### **3.4 Research Methods**

#### **3.4.1 Cluster Randomized Controlled Trial Design**

This study employs a multicenter, parallel, pragmatic cluster randomized controlled trial (cRCT) design, implemented across 30 primary care centers in Xicheng District, Beijing. A cluster design is chosen to minimize contamination between treatment arms and to align with the natural unit of CDSS implementation at center level. Each of the 30 community health service centers/stations constitutes a cluster.

#### **3.4.2 Randomization and Intervention Allocation**

Stratified cluster randomization is employed at center level. Prior to the study, the 30 centers are stratified into three categories based on annual outpatient visit volume: large ( $\geq 10,000$  visits/year), medium (1,000–9,999 visits/year), and small ( $< 1,000$

---

visits/year). Within these strata, an independent statistician uses a computerized system to randomly assign centers in a 1:1 ratio to the intervention group (CDSS plus usual care) or the control group (usual care alone). Randomization results are concealed until the start of the intervention assignment.

### **3.4.3 Training Period**

Prior to the formal study period, a government-supported training program will be implemented. Following randomization, nephrologists will provide standardized on-site training at all centers on CKD management. At intervention centers, technical staff will additionally train PCPs on CDSS use and integration. This will be followed by a dedicated run-in period during which the CDSS is activated and PCPs receive on-site support; data from this phase will be excluded from the final analysis to establish routine system use.

### **3.4.4 Study Duration and Phases**

The 36-month intervention period are divided into two phases: (1) an initial six-month evaluation (Phase 1) for process measures and short-term clinical outcomes, and (2) a three-year evaluation (Phase 2) for long-term outcomes, with a composite of kidney and cardiovascular hospitalization rates as the primary endpoint.

### **3.4.5 Blinding**

Due to the pragmatic nature of the intervention, blinding of participating PCPs and patients is not feasible. However, outcome assessors and statisticians will be blinded to group allocation throughout the analysis.

### **3.4.6 Informed Consent**

The study received ethical approval from the Peking University First Hospital (2022 Study 489) and the Xicheng District Health Commission (2021 Study 104). The ethics committee granted a waiver for individual patient informed consent, as the intervention was implemented at center level, posed minimal risk by adhering to guideline-based care, and did not alter routine care. This waiver was granted on the condition that we obtained prior administrative approval from all involved community health authorities.

### **3.4.7 End of the Trial**

The trial is planned to conclude 36 months. Upon completion, all centers will be considered to have fulfilled the trial requirements, and the study database will be locked. A trial completion notice will be submitted to the ethics committee. Premature termination may occur under the following circumstances: mandatory request from the ethics committee, recommendation from the data monitoring committee, or discontinuation of trial funding.

## **3.5 Data Management**

---

Study data are generated from the EHR and LIS of community medical centers in Xicheng District, Beijing. All data are managed and stored by the “Joint Laboratory” established collaboratively by the Xicheng District Smart Health Research Center and Peking University First Hospital for community health and medical big data research.

### **3.5.1 Data Collection and Management**

Prospective data collection will be conducted via the Xicheng District Health Commission data platform linked to the CDSS application server. Following community-developed CDISC-CRF standards, EHR and LIS data will be automatically extracted to generate electronic case report forms (eCRF). After privacy-preserving de-identification, data were synchronized daily (T+1) via a dedicated medical network to the Joint Laboratory to create the research dataset. The PostgreSQL-based research database includes structured domains for patient visits, diagnoses, prescriptions, clinical notes, vital signs, and laboratory reports, with standardized coding applied to diagnoses, medications, and laboratory data to enhance research usability.

The study endpoint—hospitalization rates for kidney-related or cardiovascular events among CKD patients—will be assessed by linking with the Beijing Municipal Inpatient Medical Insurance Database. This database provides comprehensive and auditable hospitalization records for Beijing-insured patients admitted to tertiary hospitals, including demographics, treatments, clinical diagnoses (ICD-10 coded), costs, and department information.

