#### **2.2.2 Secondary Objectives**

##### **Process Measures:**

1. To assess the effect of the CDSS on the underdiagnosis of CKD, as measured by the rate of appropriate ICD-coded documentation in patient records.
2. To examine the change in the utilization rates of renoprotective medications (RAASi and sodium-dependent glucose transporters 2 inhibitor [SGLT2i]) among CKD patients.
3. To evaluate the impact of the CDSS on the screening rate for CKD (SCr and/or urine protein testing) among patients at high risk for CKD.
4. To determine the effect of the CDSS on the referral rate of CKD patients who meet guideline-based criteria for nephrology consultation.

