##### 3.1.2 CKD Patients

###### 3.1.2.1 Inclusion Criteria

1. Age $\geq$ 18 years

- 
2. Diagnosis of CKD, defined as meeting at least one of the following criteria:
- (1) Two estimated glomerular filtration rate (eGFR) values  $<60 \text{ mL/min/1.73m}^2$  (calculated using the CKD-EPI equation), obtained  $\geq 90$  days apart.
  - (2) Confirmed proteinuria, defined as two positive results  $\geq 90$  days apart for either urine albumin-to-creatinine ratio (UACR)  $\geq 30 \text{ mg/g}$ , urine dipstick  $\geq 1+$ , or 24-hour urine total protein (UTP)  $\geq 150 \text{ mg}$ .
  - (3) Documented CKD diagnostic codes in the EHR, supplemented by at least one qualifying eGFR or proteinuria result meeting the above thresholds.

3. Beijing medical insurance residents.

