### **3.1.3 High-risk Patients for CKD**

#### **3.1.3.1 Inclusion Criteria**

1. Age  $\geq 18$  years

2. No established diagnosis of CKD

3. Presence of at least one of the following risk factors:

(1) Type 2 diabetes mellitus (T2DM) (ICD-coded)

(2) Hypertension (ICD-coded)

(3) Cardiovascular disease (ICD-coded)

(4) Obesity: body mass index (BMI)  $\geq 28.0 \text{ kg/m}^2$  per Chinese expert consensus, or relevant ICD-10 codes.

(5) History of AKI/AKD: meeting either KDIGO SCr criteria or a clinical diagnosis, as detailed in **Table 3**

(6) Kidney stones (ICD-coded)

(7) Family history of kidney disease

(8) Advanced age ( $>60$  years)

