## **3.3 Study Outcomes**

### **3.3.1 Main Outcomes**

1. Hospitalization rates for kidney-related (acute kidney injury, progression of kidney disease, or requiring dialysis) or cardiovascular events including myocardial infarction, stroke, heart failure, or cardiovascular procedures) among CKD patients.

2. Hospitalization rates for kidney-related events in patients at high-risk for CKD

Data sources for main outcomes: Electronic medical record systems of community medical institutions and Beijing medical insurance claims database.

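### Main outcome 2 does not limit its cohort to patients the linked claims database can see, and sections 3.3.1 and 3.5.1 name different event sources for the main outcomes

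*Protocol*

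**What the plan says.** **Eligibility.** Section 3.1.2.1 requires CKD patients to be "Beijing medical insurance residents". For the high-risk cohort, 3.1.3.1 asks for adult age, no established CKD and "Presence of at least one of the following risk factors". It has no insurance item. Section 3.1.3.2 takes over the CKD exclusions (pregnancy, malignancy, end-stage kidney disease), and 3.1.1 adds two visits in the screening year. Neither adds insurance.

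**Outcomes and sources.** Section 3.3.1 defines main outcome 1 as kidney-related or cardiovascular hospitalisation in CKD patients, and main outcome 2 as kidney-related hospitalisation in high-risk patients. For both it states: "Data sources for main outcomes: Electronic medical record systems of community medical institutions and Beijing medical insurance claims database". Section 3.5.1 speaks only of "hospitalization rates for kidney-related or cardiovascular events among CKD patients", which "will be assessed by linking with the Beijing Municipal Inpatient Medical Insurance Database", and describes that database as holding "hospitalization records for Beijing-insured patients admitted to tertiary hospitals". Section 3 (Research Design) refers to linkage with a centralised Beijing insurance database and mentions no tertiary limit.

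**The intervention and the community record.** The CDSS is built into the community EHR in intervention centres only (section 3). One of its aims, in 2.2.2, is to reduce underdiagnosis, "as measured by the rate of appropriate ICD-coded documentation in patient records". Section 3.4.5 says that outcome assessors and statisticians are blinded.

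**The concern.** There are two separate problems.

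First, the denominator of main outcome 2 does not match its data source. An uninsured high-risk patient meets 3.1.3.1 but cannot appear in the claims. If such patients stay in the analysis, they contribute follow-up in which no claims event can be seen. The only other named source for them is the community record.

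Second, the event definition is open. An analyst following 3.3.1 could count admissions noted in community records; one following 3.5.1 would count claims only. The choice matters because the CDSS is meant to alter testing, coding and referral in the community record in one arm. Kidney events such as acute kidney injury or disease progression depend on testing and coding. If community entries count, more events might be found in intervention centres for the same underlying rate, which would hide a benefit.

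**Working it through.** The plan gives no figure for coverage, insured share or share of admissions outside tertiary hospitals. The check is therefore a comparison of the sections, followed by arithmetic on assumed capture.

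**1. Sections side by side**

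| | CKD cohort (main outcome 1) | High-risk cohort (main outcome 2) |
|---|---|---|
| Insurance required | Yes (3.1.2.1) | No (3.1.1, 3.1.3.1, 3.1.3.2) |
| Sources in 3.3.1 | Community records and claims | Community records and claims |
| Source in 3.5.1 | Inpatient insurance database | Not mentioned |

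The insurance gap therefore concerns main outcome 2 only. The source conflict concerns both.

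**2. Formula.** If a share c of true events is captured in an arm, its observed rate is c × true rate. Hence observed rate ratio = true rate ratio × (c in intervention ÷ c in control).

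**3. Equal capture.** The two shares cancel, so a true ratio of 0.80 is observed as 0.80.

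- *Main outcome 2.* If a share u of person-time in each arm is uninsured, and event rates are the same with and without insurance, the claims rate is (1 − u) × the true rate. For assumed u of 0%, 5%, 10% and 15%, that is 100%, 95%, 90% and 85% of the true rate in each arm. The ratio does not change; the absolute rates and their difference are too small. Section 3.6.1 gives no rate or power for this outcome, so a power loss cannot be computed.
- *Main outcome 1.* Only the tertiary limit applies. Inputs from 3.6.1: 35.0 per 100 person-years, a 20% reduction (0.35 × 0.80 = 0.28), 36 months (3 person-years each), 3,240 patients in 30 centres (108 per centre, 1,620 per arm), ICC 0.02, alpha 0.05 (two-sided assumed). Design effect = 1 + (108 − 1) × 0.02 = 3.14. In a normal approximation for two rates, z = 0.07c ÷ √[(0.63c ÷ 3) × 3.14 ÷ 1,620] − 1.96. At c = 1, z = 0.0700 ÷ 0.0202 − 1.96 = 1.51, a power of 93% against the stated 90%. This approximation does not reproduce the plan's online calculator; it serves only to show the trend. Power is 91% at c = 0.90, 87% at 0.80, 77% at 0.60 and 69% at 0.50.

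**4. Unequal capture (assumed values).**

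| Extra relative capture, intervention arm | True 0.80 observed as | True 1.00 observed as |
|---|---|---|
| 0% | 0.80 × 1.00 = 0.80 | 1.00 |
| 5% | 0.80 × 1.05 = 0.84 | 1.05 |
| 10% | 0.80 × 1.10 = 0.88 | 1.10 |

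At 10%, (0.88 − 0.80) ÷ (1.00 − 0.80) = 40% of the planned reduction disappears. At 5% it is 20%.

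**The case against.** A reader might infer that both main outcomes are ascertained unevenly between the arms. The documents do not support that:

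- CKD patients must be Beijing-insured, so the insurance gap cannot affect main outcome 1.
- The insurance and tertiary limits hold in both arms, and equal under-capture leaves the rate ratio alone.
- No section says that a community entry alone counts as a hospitalisation. The coding objective in 2.2.2 concerns a CKD diagnosis label, not an admission. Section 3.3.1 can be read as community records for cohort and covariates, and claims for events. A source hierarchy may stand in an SAP that is not shown.
- The tertiary limit appears in 3.5.1 alone.

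Two further readings are tempting. One is that uninsured shares differ between arms: an assumed 5% in control and 15% in intervention would give 0.85 ÷ 0.95 = 0.89 with no true effect. Nothing in the plan suggests such a split. Patients are selected from screening-year visits, and a CDSS does not change insurance status. An imbalance across 30 centres would be chance and could run either way. The other is that CDSS-driven referral moves admissions into tertiary hospitals and so raises capture in one arm. That is conceivable, but the plan says nothing about the level of hospital to which patients are admitted.

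All of this stands against a claim of established bias. It does not remove the two textual faults. Eligibility belongs in the protocol, which applies the insurance criterion to one cohort and omits it for the other. Sections 3.3.1 and 3.5.1 name different sources. Blinded assessors cannot restore events that were never recorded in control centres. How unlinkable patients are handled is not stated, so their person-time in the denominator follows from the eligibility text rather than from an explicit rule.

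**Conclusion.** The point holds in this form. The cohort for main outcome 2 is not restricted to patients whose admissions the linked database can show, and the event sources for the main outcomes are stated inconsistently, with 3.5.1 silent on main outcome 2.

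The certain consequence is limited: under-counting and unobservable person-time for whatever share of high-risk patients is uninsured, which may be small. The possible consequence is larger: if community records supply events, a record system altered by the CDSS in one arm feeds the main outcomes. The range of 0.80 to 0.88 for a true 0.80 rests on assumed excess capture of 0% to 10%; equal capture gives no bias. The 20% reduction is planned for the CKD composite, so that range should not be read as a forecast for main outcome 2.

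**What to change.** 1. Add "Beijing medical insurance residents" to the inclusion criteria in 3.1.3.1, and count person-time for main outcome 2 only while the patient is insured.
2. Reconcile 3.3.1 with 3.5.1. Define hospitalisation events for both main outcomes from insurance claims alone, in both arms; use community records for cohort definition and covariates. Name main outcome 2 in 3.5.1.
3. Establish whether the database is really limited to tertiary hospitals. If it is, name the endpoint as tertiary-hospital admissions in 3.3.1 and limit the conclusion accordingly. Claims-only events would not remove a shift in admission level, so this wording is needed as well.

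These changes should be settled before outcome data are linked, so that the choice of source cannot depend on results. A stated hierarchy of sources would also resolve the contradiction, but it would leave a source that the intervention alters able to supply events.

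The cost is wording in three sections, a slightly smaller high-risk cohort and, if the tertiary limit is real, a narrower stated endpoint. Admissions noted only in community records would no longer count.

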### **3.5.2 Data Governance**

Raw data collected from community CDSS servers will undergo comprehensive governance to ensure suitability for research and eCRF generation. Key steps include dictionary normalization, cleaning of unstructured text, semantic parsing and association, and systematic data quality control.

### **3.5.3 Data Security and Quality Control**

The data management team plans to use several security steps to protect information, including firewalls, systems to prevent data leaks, network monitoring, and activity logs. Data quality will be checked during the entire process—from collection and cleaning to merging and updating. Automated tools will be adopted to complete missing values and correct errors to ensure that the data are complete, standardized, consistent, and accurate. A Data and Safety Monitoring Committee (DSMC) carries out regular quality checks, provides feedback, creates quality reports, and helps to resolve any data issues promptly.

### **3.5.4 Data Usage**

This study will strictly follow national and industry rules for data security. All researchers accessing data are required to sign confidentiality agreements, managed

---

by the DSMC. Electronic audit trails will record all data entries and modifications, including reasons, timestamps, and user identifiers.

## **3.6 Statistical Analysis**

### **3.6.1 Sample Size and Statistical Power**

The primary outcome is a composite hospitalization rate for kidney-related (acute kidney injury, progression of kidney disease, or requiring dialysis) or cardiovascular events (myocardial infarction, stroke, heart failure, or cardiovascular procedures). Based on data from the US CRIC cohort, the all-cause hospitalization rate for CKD patients is 35.0 per 100 person-years. The sample size calculation aims to detect a 20% reduction in this rate following 36 months of CDSS intervention, compared to usual care. The calculation is performed using cluster randomization tools (online calculator at <https://clustercts.shinyapps.io/rshinyapp/>) with the following parameters: 30 randomized centers (15 per arm), an intraclass correlation coefficient of 0.02, and a significance level of 0.05. A total sample size of 3,240 participants is estimated to provide 90% statistical power (**Figure 1**).

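### The 90% power claim for the kidney/cardiovascular endpoint rests on an all-cause hospitalisation rate, so it is unsupported

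*Protocol*

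**What the plan says.** Protocol Section 3.3.1 gives the first main outcome, in CKD patients, as "Hospitalization rates for kidney-related (acute kidney injury, progression of kidney disease, or requiring dialysis) or cardiovascular events", the cardiovascular part being myocardial infarction, stroke, heart failure and procedures. Section 3.6.1 repeats this ("The primary outcome is a composite hospitalization rate for kidney-related" and so on) and then turns to a different quantity for the control rate: "Based on data from the US CRIC cohort, the all-cause hospitalization rate for CKD patients is 35.0 per 100 person-years". The target is to "detect a 20% reduction in this rate following 36 months of CDSS intervention", so both the base rate and the effect refer to all-cause admissions. The other inputs are 30 centres split 15 and 15, with "an intraclass correlation coefficient of 0.02, and a significance level of 0.05". The result is: "A total sample size of 3,240 participants is estimated to provide 90% statistical power". No kidney/cardiovascular admission rate appears anywhere in the protocol.

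**The concern.** Within one paragraph the endpoint is cause-specific and the rate that powers it is all-cause. In any one population the listed admissions cannot outnumber all admissions, so the mismatch runs in one direction: too many events are expected and power is overstated. Section 3.5.1 adds a further reason to doubt that the rate carries over, since it describes the linked database as recording admissions to tertiary hospitals.

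This is the power statement for the primary endpoint of a 36-month trial in 30 centres. If the result is inconclusive, readers will weigh it against a 90% that was calculated for another outcome.

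**Working it through.** **Inputs from Section 3.6.1.** All-cause rate 35.0 per 100 person-years; 20% reduction, giving 28.0; 36 months; 15 centres per arm; ICC 0.02; alpha 0.05; N = 3,240.

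**Assumptions added here.** Two-sided test, equal centres, Poisson counts, three full years per patient. No dropout or overdispersion is included, because none is stated.

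**1. Reproducing the stated figure**
- Patients per centre: 3,240/30 = 108. Per arm: 1,620.
- Design effect: 1 + (108 − 1) × 0.02 = 3.14.
- Three-year mean counts: 1.05 (control) and 0.84 (CDSS).
- Test ratio: (1.05 − 0.84) / √[(1.05 + 0.84) × 3.14/1,620] = 3.47.
- Power: 93.4% by the normal reference, 91.7% by t on 28 df.

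So the stated 90% is roughly recovered, and it needs the all-cause rate. (Exactly 90% would need about 2,209 patients by normal or 2,676 by t.)

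**2. What happens at a lower composite rate**

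The protocol gives no composite rate, so a range is assumed: 33% to 60% of the all-cause rate, or about 11.6 to 21 per 100 person-years. The answer also depends on how between-centre variation behaves when the mean count falls.

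*Model A: ICC stays at 0.02.* The variance of the difference is (μ₁ + μ₂) × 3.14/1,620.
- At 21 per 100 person-years: counts 0.63 and 0.504; ratio 0.126/√(1.134 × 3.14/1,620) = 2.69; power 74%.
- At 11.55: counts 0.3465 and 0.2772; ratio 0.0693/√(0.6237 × 3.14/1,620) = 1.99; power 49%.

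*Model B: relative between-centre variation k stays constant.* Choose k so that the ICC is 0.02 at the all-cause mean of 1.05: k² = 0.02/(0.98 × 1.05) = 0.0194, so k = 0.139. The variance is (μ₁ + μ₂)/1,620 + k²(μ₁² + μ₂²)/15.
- At 21: 0.000700 + 0.000843 = 0.001543; ratio 0.126/√0.001543 = 3.21; power 87%.
- At 11.55: 0.000385 + 0.000255 = 0.000640; ratio 0.0693/√0.000640 = 2.74; power 75%.

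Power for a 20% reduction with 108 patients per centre, t on 28 df:

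| Composite per 100 person-years (share of 35.0) | Model A | Model B |
|---|---|---|
| 35.0 (100%) | 92% | 93% |
| 21 (60%) | 74% | 87% |
| 17.5 (50%) | 66% | 84% |
| 11.55 (33%) | 49% | 75% |

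**3. Break-even for 90% at 3,240 patients**
- Model A: 30.5 (normal) to 32.8 (t) per 100 person-years, which is 30.5/35 = 87% to 32.8/35 = 94% of the all-cause rate.
- Model B: about 26 by t (26/35 = 74%). The normal reference, which is optimistic with 30 centres, gives about 22 (63%).

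**4. Reduction detectable with 90% power (t, same assumptions)**
- At 21 per 100 person-years: 25% (A) or 21% (B).
- At 17.5: 27% or 22%.
- At 11.55: about 33% or 24%.

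**The case against.** The arithmetic in Section 3.6.1 is sound: its own inputs return slightly more than 90%. The fault is in an input, and the size of the loss cannot be fixed from the protocol, because neither the composite rate nor the local all-cause rate is given. That stands, and it is why ranges are shown here.

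Three stronger readings are tempting, and the document does not support them.

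- *More patients cannot restore the power, because effective sample size is capped at 750 per arm (15/0.02).* This holds only if the ICC stays at 0.02 as the event rate falls. Under model B, power at a 50% share rises from 84% at 108 patients per centre to 92% at 200, and at a 33% share it reaches 92% at 300. Nor is 3,240 a ceiling: Section 3.1.1 draws patients from all visits to the centres in the screening year.
- *The calculation assumed equal centres although volumes differ more than tenfold.* Section 3.6.1 lists no coefficient of variation for centre size, but the calculator output (Figure 1) is not shown. By t, a coefficient of about 0.31 would give exactly 90% at 3,240, so one may have been entered. The strata in Section 3.4.2, such as "medium (1,000–9,999 visits/year), and small", count outpatient visits and not eligible CKD patients. Only large and small centres must differ tenfold, and a mixed model loses less to unequal centres than the usual inflation formula suggests.
- *The rates are really 35% against 28%, which gives far lower power.* The text says person-years, so that reading is not a fair test of the claim.

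**Conclusion.** The point holds as an input mismatch. The 90% is calculated for all-cause admissions and claimed for kidney/cardiovascular admissions. It would carry over only if the composite made up at least about 87-94% of the all-cause rate (ICC fixed at 0.02) or about 74% (constant relative variation, t reference), and the protocol offers nothing to show this. For an assumed share of 33-60%, power at 3,240 patients is about 49-74% or 75-87% respectively. These figures rest on equal centres, Poisson counts, complete three-year follow-up and a two-sided test. Overdispersion, shorter follow-up or unequal centres would lower them; more eligible patients would raise them. A reader should not infer that the trial is certain to miss 90%, or that its size cannot be made adequate: the protocol settles neither.

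**What to change.** Rewrite the paragraph in Section 3.6.1:

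- Replace the all-cause rate with a kidney/cardiovascular admission rate as the linked insurance database captures it. Use the pooled, arm-blind rate in the identified CKD cohort or, if linkage is not yet done, a stated range with its source.
- State whether the ICC or the relative between-centre variation is assumed to hold at that rate.
- Use the expected number of eligible CKD patients in place of 3,240 if it differs.
- Replace the 90% with the resulting power, or give the relative reduction detectable at 90%.
- Show the observed variation in CKD patients per centre as a sensitivity analysis.

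The cost is one paragraph and a rerun of the calculator, with no change to conduct. The stated power will be less favourable.
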